**Figure 2 F2:**
[figure not shown]
The fNIRS measurement sites of the COPD group and healthy control group. COPD = chronic obstructive pulmonary disease, fNIRS = functional near infrared spectroscopy.

**Figure 3 F3:**
[figure not shown]
The intervention procedure of the healthy intervention group. (A) Moxibustion site of the Heart meridian and the fNIRS measurement sites of the Heart and Lung meridians; (B) Moxibustion site of the Lung meridian and the fNIRS measurement sites of the Heart and Lung meridians. fNIRS = functional near infrared spectroscopy.

#### Acupoint locations and fNIRS measurement sites

2.6.3

(1)“Shenmen” (HT7): On the anteromedial aspect of the wrist, radial to the flexor carpi ulnaris tendon, on the palmar wrist crease.(2)“Shaohai” (HT3): On the anteromedial aspect of the elbow, just anterior to the medial epicondyle of the humerus, at the same level as the cubital crease.(3)“Taiyuan” (LU9): On the anterolateral aspect of the wrist, between the radial styloid process and the scaphoid bone, in the depression ulnar to the abductor pollicis longus tendon.(4)“Chize” (LU5): On the anterior aspect of the elbow, at the cubital crease, in the depression lateral to the biceps brachii tendon.(5)The midpoint of the Heart meridian along the forearm: the midpoint between HT3 and HT7.(6)The midpoint of the Lung meridian along the forearm: the midpoint between LU5 and LU9.

#### Concomitant treatments

2.6.4

Participants in the COPD group will maintain current treatments during study. If new medications or therapies are added throughout the study, they should be recorded in details.

Besides, participants in the healthy group or healthy control group are not permitted to take any medications during study. If they suffer from sudden diseases and medications or other treatments are applied for emergency, corresponding information should be recorded and researchers will determine whether they will be suspended from the trial.

### Outcomes

2.7

The primary outcome will be regional oxygen saturation of the aforementioned sites that located in the Heart and Lung meridians. Second outcomes will be fundamental physiological parameters measured before and immediately after fNIRS examinations, including body temperature, heart rate, breathing rate, and blood pressure.

### Safety evaluation

2.8

Adverse events that occur during the trial will be documented and assessed by researchers. If serious adverse events occur, they should be reported to the ethics committee by researchers immediately and remedial measures should be adopted in time.

### Ethics approval

2.9

This study has been approved by the Ethics Committee of the Third Affiliated Hospital of Zhejiang Chinese Medical University (approval number. ZSLL-KY-2019-001F-01). Informed consent will be signed by the participants before they are included in the study.

### Trial registration

2.10

The trial has been registered at clinical trials (identification code NCT04046666).

### Data collection and statistical analysis

2.11

SPSS 17.0 for Windows (SPSS Inc., Chicago, IL) will be used to perform statistical analysis. For data expression, numeric data in normal distribution will be presented as mean and standard deviations, and data in skewed distribution will be presented as median and interquartile ranges. For statistical analysis methods, change in continuous variables at different time points will be analyzed by repeated measures analysis of variance. The changes within the groups will analyzed via the paired samples *t*-test, whereas differences between the groups will be compared via the independent samples *t*-test. If data is in skewed distribution, nonparametric test will be applied to perform within-group or between-group comparison. Statistical significance is defined as a *P*-value less than .05.

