### Sample size calculation

2.2

This study is a clinical trial that aims to measure the biological characteristics of meridians in COPD patients and healthy adults. Compared with common clinical trials that intend to evaluate the effectiveness of a specific therapy, there is no consensus on the standardization of sample size estimation for this kind of study. Thus, the sample size estimation is mainly according to similar trials^[15,16]^ and our preliminary study.^[12]^ Finally, the total number of participants is 120, and they will be divided into the COPD group, healthy control group, and healthy intervention group in a 1:1:1 ratio.

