1)Moxibustion in the Heart meridian: a moxa stick is ignited and inserted into a homemade holder to adjust appropriate height and angle, moxibustion is applied at acupoint HT3 of the Heart meridian for 15 minutes. The fNIRS probes will be attached to 3 measurement sites during moxibustion, including the midpoint of the Heart meridian along the left forearm (i.e. the midpoint between HT7 and HT3), the midpoint of the Lung meridian along the forearm (i.e. the midpoint between LU5 and LU9), and LU5 of the Lung meridian. The procedures for intervention and the measurement places of the fNIRS probes are shown in Figure 3A. The measurement time points consist of 5 minutes before moxibustion, 15 minutes during moxibustion, and 5 minutes after removing moxibustion.2)Moxibustion in the Lung meridian: moxibustion is applied at acupoint LU5 of the Lung meridian. The moxibustion procedure, fNIRS examinations and assessment time points are consistent with 1). The fNIRS probes will monitor oxygen saturation in 3 measurement sites synchronously during moxibustion, including the midpoint of the Lung meridian along the forearm (ie, the midpoint between LU5 and LU9), and the midpoint of the Heart meridian along the left forearm (ie, midpoint between HT3 and HT7, and HT3 of the Heart meridian. The procedures for intervention and the measurement places of the fNIRS probes are displayed in Figure 3B.

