First, as far as we are concerned, the present study is the first case-controlled trial that designed to investigate the correlation and specificity between 2 different meridians (ie, the Heart meridian and the Lung meridian) by using an objective assessment technique, fNIRS. We propose a hypothesis that during the change from the physiological to pathological state, the metabolic characteristics of the affected meridian will change synchronously. And significant difference in the metabolic characteristics might be detected between the affected meridian (ie, the Lung meridian for COPD patients) and the unaffected meridian (ie, the Heart meridian for COPD patients). Meanwhile, in the healthy control group, we put forward a hypothesis that the stimulated meridian will present with more significant change in the metabolic characteristics in relative to the non-stimulated meridian. Given that a previous study revealed that thermal stimulation could significant increase local oxygen saturation,^[24]^ in this study, moxibustion is selected as the stimulation modality. Specifically, on the one hand, the specificity of meridian-visceral association will be explored based on a metabolic comparison in the Heart and Lung meridians between the healthy control group and the CPPD group. On the other hand, the specificity of site-to-site association will be determined based on the comparison of the metabolic change between the 2 meridians that induced by moxibustion in the Heart meridian and Lung meridian, respectively, in the healthy control group.

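### The pre-moxibustion rSO2 recording is not used as a covariate, which gives up precision in the same-site, between-session contrast if expected session baselines are equal

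*Protocol article*

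**What the plan says.** Section 2.6.2 of the protocol article gives each healthy intervention participant two moxibustion sessions, one at HT3 on the Heart meridian and one at LU5 on the Lung meridian, more than 1 day apart. Each session uses three probe sites, and both forearm midpoints (Heart and Lung) are among them in both sessions. The recording is described as follows: "The measurement time points consist of 5 minutes before moxibustion, 15 minutes during moxibustion, and 5 minutes after removing moxibustion". So every midpoint has its own baseline in every session. The article does not state the order of the sessions.

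Section 2.11 names the methods. For time points, "change in continuous variables at different time points will be analyzed by repeated measures analysis of variance". For change, "The changes within the groups will analyzed via the paired samples" t-test. Between groups it names the independent samples t-test, and for skewed data a nonparametric test. No covariate is named, and the text does not spell out how the pre-moxibustion value enters.

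The Discussion states the aim as a "comparison of the metabolic change between the 2 meridians that induced by moxibustion" of each meridian in turn, with the hypothesis that the stimulated meridian changes more than the non-stimulated one. It places this in the healthy control group. Under section 2.6.2 only the healthy intervention group receives moxibustion, so I read it as that group.

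**The concern.** Repeated measures ANOVA treats the pre-moxibustion value as one more level of the outcome, and a test on changes subtracts it with a slope fixed at 1. Unless baseline and follow-up are almost perfectly correlated, a slope of 1 over-corrects: it adds baseline noise that a fitted slope would leave out. Site-to-site specificity is one of the two stated aims and rests on one group of about 40 people, in a study that describes its own sample as small. If a more precise analysis is available from data already being collected, the intervals for this aim will be wider than they need to be.

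**Working it through.** **Inputs from the article.** Section 2.2: "the total number of participants is 120", with the groups up to the "healthy intervention group in a 1:1:1 ratio", so 120/3 = 40 in the healthy intervention group. Section 2.11: "Statistical significance is defined as a *P*-value less than .05"; sidedness is not stated, and I take it as two-sided.

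**The plan's own figure.** The 120 cannot be reproduced. Section 2.2 says "the sample size estimation is mainly according to similar trials" and a preliminary study, and gives no effect size, SD, power or correlation. Everything below about size is therefore illustrative.

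**Set-up.** Take one midpoint site. For each person let B be the stimulated-session minus non-stimulated-session difference in the pre-moxibustion mean, and P the same difference in the mean during moxibustion. Assume B and P have the same variance (set to 1) and correlation rho. The contrast is within-person and same-site, so a fixed anatomical difference between Heart and Lung sites cancels.

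**Variances.**
- Change score, P − B: 2(1 − rho).
- P regressed on B, residual: 1 − rho².
- Ratio: (1 − rho²) / [2(1 − rho)] = (1 + rho)/2.

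**Numbers with n = 40.** The equivalent n is 40 divided by the ratio. The power column anchors on an assumed effect that the change-score paired t-test detects with 80% power (standardised change 0.454). It uses the noncentral t with 38 degrees of freedom and a variance inflation of 1 + 1/(n − 3) for estimating the slope.

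| rho (assumed) | ratio | variance reduction | equivalent n | power if adjusted |
|---|---|---|---|---|
| 0.5 | 0.75 | 25% | 53.3 | 89% |
| 0.7 | 0.85 | 15% | 47.1 | 85% |
| 0.9 | 0.95 | 5% | 42.1 | 81% |

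**Check by simulation, equal expected baselines** (20,000 runs, n = 40, no effect). Variance ratios were 0.77, 0.88 and 0.98 at rho 0.5, 0.7 and 0.9, slightly above the formula because the slope is estimated. False-positive rates were about 5% for both methods.

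**Check by simulation, unequal expected baselines.** Now suppose the two compared conditions differ at rest by delta = 0.5 SD of the paired difference and moxibustion has no differential effect. The adjusted intercept then has expectation delta × (1 − rho), not zero: 0.5 × 0.5 = 0.25, 0.5 × 0.3 = 0.15 and 0.5 × 0.1 = 0.05 at the three values of rho. The simulation gave 0.251, 0.150 and 0.051.

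| rho (assumed) | false positives, change score | false positives, adjusted | variance ratio |
|---|---|---|---|
| 0.5 | about 5% | 36% | 0.96 |
| 0.7 | about 5% | 21% | 1.10 |
| 0.9 | about 5% | 9% | 1.22 |

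Adjustment helps in the first setting and misleads in the second. What separates them is whether the expected baseline difference is zero.

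**The case against.** The strongest objection is that the article's own contrast may not be the one in which adjustment is safe. A comparison of change between the two meridians can be read as Heart sites against Lung sites in the same person. Those sites are anatomically different and not randomised, so resting rSO2 may differ, and the second simulation then applies: the change score is sound and the adjusted analysis is not. This stands. A reader might infer that baseline adjustment is never less precise here, or that it costs only a degree of freedom. Neither holds for a cross-site comparison. Even the same-site version needs equal expected session baselines, which the article does not secure, since it gives a washout of more than 1 day but no session order.

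Second, section 2.11 is one condensed paragraph, and covariates are often left to an analysis plan, which is not shown here. This stands in part. The point rests on the methods the article does name, none of which, as described, uses a covariate. It does not show that the full plan lacks one; if that plan already adjusts, a clarifying sentence settles the matter.

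Third, the gain is of unknown size. Day and probe-placement effects shared across one recording could push rho high, and at 0.9 the gain is about one power point. Against that, the relevant rho is between session differences, from which stable between-person variation has already been removed, so a high raw correlation between before and during does not by itself imply a high rho. Neither argument fixes the value.

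A reader might also argue that rSO2 is a percentage with a ceiling, so that the rise must depend on the starting value. Nothing in the article places forearm rSO2 near 100%, and a linear covariate would not properly resolve a ceiling effect. I do not rely on it.

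**Conclusion.** The point holds in a limited, conditional form. For the same-site, between-session contrast at each midpoint, the methods named in section 2.11 leave unused a baseline that section 2.6.2 already collects. Using it as a covariate would reduce the variance by (1 − rho)/2 of the change-score variance. That is 25%, 15% and 5% at assumed rho of 0.5, 0.7 and 0.9, less a small cost for estimating the slope. This rests on equal expected session baselines, equal variances before and during, and a rho that the documents do not give.

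A reader might infer that the planned tests are wrong or biased. The documents do not support that: repeated measures ANOVA and paired tests of change are valid methods, and for a direct Heart-site versus Lung-site comparison the change score is the safer choice. The study calls itself an exploratory pilot and makes no power claim that this would overturn. It is a worthwhile, nearly free gain in efficiency and not an error.

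**What to change.** In section 2.11, for the healthy intervention group:

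- Define the contrast at each midpoint as the within-person difference, stimulated session minus non-stimulated session, in mean rSO2 during moxibustion, and separately after removal.
- Regress that difference on the same site's pre-moxibustion session difference and test the intercept.
- Balance session order, or include it as a term coded symmetrically around zero so that the intercept remains the average effect.
- Keep the paired test on change scores as a sensitivity analysis, and make it the main analysis for any direct Heart-site versus Lung-site comparison.

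The cost is a few sentences and a standard regression. If session order is modelled instead of balanced, no new measurements or participants are needed. The downsides are one or two degrees of freedom, reliance on equal expected session baselines, and a negligible gain if rho is about 0.9 or higher.

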### Quality control

2.12

This protocol has been revised based on suggestions of experienced acupuncturists before conducting the trial. All researchers will receive intensive training courses to master the standard operating procedures. Procedures of fNIRS examinations will be trained by specific experts in this field. Case report forms will be verified by monitors at regular intervals throughout the study. In addition, economic compensation will be adopted to improve participant compliance and reduce dropouts.

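### For the moxibustion data, a linear mixed model would keep partial records that a repeated-measures ANOVA across sessions or sites discards; the gain is modest and cheap

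*Protocol article*

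**What the plan says.** Section 2.11 (Data collection and statistical analysis) fixes the method for time courses: "change in continuous variables at different time points will be analyzed by repeated measures analysis of variance". The same section adds paired and independent t-tests, with nonparametric alternatives for skewed data. On within-group change it says: "The changes within the groups will analyzed via the paired samples *t*-test". The software is named ("SPSS 17.0 for Windows (SPSS Inc., Chicago, IL) will be used to perform statistical analysis"), and so is the threshold ("Statistical significance is defined as a *P*-value less than .05"). The section does not say which factors enter the ANOVA, how the recordings are summarised over time, or whether a sphericity correction is applied.

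Section 2.6.2 (Procedures for the fNIRS examinations and moxibustion) gives the structure of the data. Each healthy intervention participant has one session with moxibustion at HT3 and one at LU5, separated by more than 1 day. Three sites are recorded at once in each session. The two forearm midpoints are common to both sessions. The third site is LU5 in the Heart session and HT3 in the Lung session. On timing: "The measurement time points consist of 5 minutes before moxibustion, 15 minutes during moxibustion, and 5 minutes after removing moxibustion".

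Section 2.2 (Sample size calculation) sets 120 participants, allocated equally (1:1:1) to the three groups. Losses are touched on twice. Section 2.12 (Quality control) says "economic compensation will be adopted to improve participant compliance and reduce dropouts". Section 2.6.4 (Concomitant treatments) says of healthy participants who need emergency treatment that "researchers will determine whether they will be suspended from the trial".

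**The concern.** The Discussion (Section 3) hypothesises that the stimulated meridian changes more than the non-stimulated one. It places this in the healthy control group, but under Section 2.6.2 only the healthy intervention group receives moxibustion. The hypothesis is therefore tested within one arm of about 40 people, and it is a phase-by-meridian interaction.

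Every completed session contains that comparison in full, because both meridians are recorded at the same time. A classical repeated-measures ANOVA covering both sessions, or several sites, nevertheless drops a person who lacks any one modelled cell. Two visits on different days make a missed session plausible. The third site also differs between sessions, so site and session are not fully crossed. The ANOVA must relabel or omit sites, whereas a mixed model takes the data as collected.

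A second, separate issue is that the univariate F test assumes sphericity, meaning equal variances of the differences between phases. Person-to-person variation in the response to heat, present mainly in the middle phase, can violate it and make an uncorrected test anti-conservative.

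**Working it through.** **Inputs from the article.** 120 participants at 1:1:1 give 120/3 = 40 in the moxibustion arm. There are 2 sessions, 3 sites per session and 3 phases. Alpha is 0.05. The article gives no effect size, standard deviation, power or dropout rate, so the 120 cannot be reproduced from a formula; only the 40 per group can be checked.

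**Assumptions.** 10% or 20% of participants (4 or 8 of 40) miss one phase or one session, at random. The mixed model is taken as a likelihood analysis with known covariance.

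**1. One phase missing (say the last) at one site.** The complete-case analysis of the during-minus-before contrast uses 36 or 32 people; the mixed model uses all 40. The ratio of standard errors is √(40/n):

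- 10%: √(40/36) = 1.054
- 20%: √(40/32) = 1.118

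For the contrast that involves the missing phase, the ratio is only 1.013 to 1.020 (10%) and 1.027 to 1.041 (20%), for correlations between phases of 0.9 down to 0.3.

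**2. One session missing, split evenly between the two sessions.** The outcome is the within-session difference in change, stimulated minus non-stimulated. With correlation r = 0 between sessions, each session is seen in 38 or 36 people, against 36 or 32 complete cases:

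- 10%: √(38/36) = 1.027
- 20%: √(36/32) = 1.061

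With r above 0:

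| r | Missing | Average of sessions | Difference of sessions |
|---|---|---|---|
| 0.3 | 10% | 1.035 | 1.019 |
| 0.3 | 20% | 1.078 | 1.043 |
| 0.6 | 10% | 1.043 | 1.011 |
| 0.6 | 20% | 1.095 | 1.025 |

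Across cases 1 and 2 the penalty runs from about 1% to about 12%.

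**3. Dependence on layout.** If whole session-by-site recordings are lost independently at 2% or 5% (assumed), the number of complete cases is 40(1 − p)^k, where k is the number of recordings in the ANOVA:

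- one site, k = 1: 39.2 or 38.0
- three sites of one session, k = 3: 37.6 or 34.3
- all six recordings, k = 6: 35.4 or 29.4

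With k = 1, a dropped person has no data at that site, so a mixed model of that site alone recovers nothing.

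**4. Sphericity.** Simulation with n = 40 and three phase means of unequal length covered a grid of assumed serial correlations and person-to-person variation in response:

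| Setting | Epsilon | Uncorrected F | Greenhouse-Geisser | Multivariate |
|---|---|---|---|---|
| Grid | 0.65 to 0.94 | 0.051 to 0.069 | 0.047 to 0.050 | 0.048 to 0.052 |
| Near worst case | 0.5 | 0.087 | 0.051 | 0.049 |

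As a check at epsilon 0.5: the nominal 5% critical value of F(2, 78) is 3.114. Scaling the degrees of freedom by epsilon gives F(1, 39), and P(F(1, 39) > 3.114) = 0.085, in line with 0.087. Unequal phase lengths alone, with no variation in individual response, gave epsilon 0.78 to 0.93.

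**5. Does any mixed model suffice?** No. On one complete simulated data set, a random-intercept model gave F = 0.1451, identical to the repeated-measures ANOVA, so it keeps the same covariance assumption. An unstructured covariance needs 3 × 4/2 = 6 parameters for three phases, which is feasible. Over all 18 cells it needs 18 × 19/2 = 171, which is not feasible with 40 people.

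**The case against.** The strongest reply is that Section 2.11 names a standard method and leaves its settings open. Layout, sphericity correction and handling of missing recordings commonly belong in a statistical analysis plan or full protocol, and neither is shown. If each session is analysed separately, a missed second session costs the first nothing. The simplest comparison, change at the two midpoints recorded together, can be made with the planned paired t-test, which needs no sphericity. The evidence for losses is thin: one sentence on compensation and one on possible suspension after emergency treatment, with no rate. The Discussion also calls the study a pilot.

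Most of this stands, and it limits the point. A reader might infer that the plan drops every participant with any missing recording, down to 35 or 29 of 40. That requires all six recordings in one ANOVA and assumed loss rates, and the article specifies neither. A reader might infer that the P values will be wrong. That holds only if an uncorrected F test is reported, and a Greenhouse-Geisser or multivariate test is still repeated-measures ANOVA. A reader might infer bias from complete-case analysis. Nothing here demonstrates it: the loss assumed above is random, and a mixed model is also biased if data are missing not at random.

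The reply does not remove the main observation. The article has chosen the method, not left it open. Analyses run separately by site cannot test the between-meridian difference. A sphericity correction does not bring back people excluded for incomplete data.

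**Conclusion.** The point holds as a recommended improvement, not as an error in the plan. For an ANOVA that spans sessions or sites, complete-case exclusion would enlarge the standard error by about 1-12% if 10-20% of participants miss one phase or session. Those rates and the covariances are assumptions. With narrower layouts the loss shrinks, and for a single site with whole recordings lost it vanishes. The type I error of about 5-7% for three phases, or about 9% near epsilon 0.5, applies only to an uncorrected F test and has remedies within repeated-measures ANOVA. The case for changing rests on the low cost and on the fact that this one arm of about 40 carries the moxibustion hypothesis.

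**What to change.** In Section 2.11, for the moxibustion analysis, replace repeated-measures ANOVA by a linear mixed model (SPSS MIXED, REML):

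- **Fixed effects:** phase, site, stimulated versus non-stimulated meridian, session (which meridian was treated), and the phase-by-stimulated-meridian interaction. The interaction is the test of the Discussion's hypothesis; a main-effects model would not estimate it.
- **Random effects:** participant, and session within participant.
- **Covariance:** unstructured over the three phase means (6 parameters), with a simpler heterogeneous structure named in advance as the fallback.
- **Population:** every participant with at least one recorded session.

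One detail to settle at the same time: LU5 and HT3 are recorded only when they lie on the non-stimulated meridian. A phase-by-site term, or a supporting analysis of the two midpoints alone, would keep the comparison like for like.

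The cost is a change of wording and slightly more analysis work, with no extra participants or measurements. The drawbacks are possible convergence problems and, for incomplete records, validity only under missing at random. If repeated-measures ANOVA is kept, state the layout and commit to a Greenhouse-Geisser or multivariate test. That settles the type I error but not the lost records.

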Second, based on comparison upon the metabolic differences of the Heart and Lung meridians in healthy adults and COPD patients, it will verify whether fNIRS is validated as an add-on technique to assist diagnosis of specific diseases that affects oxygen metabolism in tissue, such as COPD. Previous studies revealed that low oxygen saturation could be detected in peripheral vessels in COPD patients.^[29–31]^ Similarly, based on the theory of meridian-viscera association in traditional Chinese medicine, pathological changes of internal organs will manifest in the external regions or acupoints that belongs to the diseased meridian, and this phenomenon is confirmed by a number of modern studies.^[32,33]^ Nevertheless, it remains unclear whether the distribution regions of the Lung meridians present with abnormal oxygen metabolism in relative to distribution regions of the other meridians or non-meridian paths, which will be verified by the findings of our study.

Third, various kinds of measures will be made to minimize the confounding factors that affect the tissue oxygen metabolism. In details, an experimental room with controlled temperature and humidity is set up and participants are asked to rest for a long period to adapt to the environment. All fNIRS examinations are performed at about the same period of the day. Meanwhile, stimulating food or drink, and exercise are restricted before fNIRS examinations. Fundamental physiological parameters will be measured before and immediately after fNIRS examinations, with the aim to eliminate the possibility that the change of oxygen metabolism is resulted from significant change of fundamental physiological parameters in normal state. Moreover, in order to minimize individual differences, the ratio of participant gender is controlled as 1:1 and the age between the COPD group and the healthy group will try to be matched as much as possible.

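### Meridian specificity in COPD is a group-by-meridian question, but the analysis section names no such contrast, so general desaturation or site anatomy can pass as specificity

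*Protocol article*

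**What the plan says.** **Question.** The Abstract and the Discussion set two aims. The first (hypothesis 1, meridian-visceral specificity) compares the Heart and Lung meridians between COPD patients and healthy controls. The second (hypothesis 2, site-to-site specificity) compares the change after moxibustion between the two meridians.

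**What counts as support.** For COPD patients the Discussion expects that a "significant difference in the metabolic characteristics might be detected between the affected meridian" (Lung) and the unaffected one (Heart). For moxibustion it expects that "the stimulated meridian will present with more significant change in the metabolic characteristics in relative to the non-stimulated meridian".

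**Tests.** Section 2.11 assigns repeated measures ANOVA to change across time points and paired t-tests to changes within groups, and it states that "differences between the groups will be compared via the independent samples" t-test. Nonparametric tests replace these for skewed data. Significance is a P "value less than .05". No between-meridian contrast and no group-by-meridian or stimulation-by-meridian term appears.

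**Rival explanation.** The Discussion itself reports that "low oxygen saturation could be detected in peripheral vessels in COPD patients".

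**Data.** Section 2.6.2 records HT3, HT7, LU5 and LU9 synchronously for 10 minutes in the COPD and healthy control groups. Each participant in the healthy intervention group has one Heart and one Lung moxibustion session.

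**The concern.** Specificity means that COPD shifts the Lung meridian by a different amount from the Heart meridian. That is a difference of differences, and neither comparison that the article points to estimates it:

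- COPD versus healthy at the Lung sites combines any meridian effect with the general desaturation that the article acknowledges.
- Lung versus Heart within COPD combines it with anatomy. Section 2.6.3 places the Lung points and the Heart points on different aspects of the wrist and elbow, so their rSO2 need not be equal in anyone, healthy or ill.

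Specificity is the study's central claim. With these tests it could be reported when COPD lowers both meridians equally, or when the sites simply differ in every participant.

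**Working it through.** **Inputs from the article.** Section 2.2: "Finally, the total number of participants is 120", split between the COPD group, "healthy control group, and healthy intervention group in a 1:1:1 ratio", so 120/3 = 40 per group. The total cannot be reproduced: "the sample size estimation is mainly according to similar trials" and a preliminary study, with no effect size, SD or power given. Alpha is 0.05; two-sided is assumed.

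**Assumed inputs (not in the article).** SD = 1 for a participant's meridian value; Lung-Heart correlation ρ = 0.3-0.7; COPD deficit g = 0.3-0.7 SD, equal at both meridians; anatomical Lung-Heart offset a.

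**Step 1: what each comparison estimates.** Let s be a true Lung-specific effect of COPD. Expected values:

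| | Heart | Lung |
|---|---|---|
| Healthy control | μ | μ + a |
| COPD | μ − g | μ + a − g + s |

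- Lung, COPD minus healthy: s − g.
- Lung minus Heart within COPD: a + s.
- (Lung minus Heart) in COPD minus the same in healthy: (a + s) − a = s.

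Only the third isolates s.

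**Step 2: general desaturation with s = 0.** The independent t-test at a Lung site has noncentrality g√(40/2). At g = 0.5 this is 0.5 × 4.47 = 2.24, and the test is significant in about 60% of trials. The table gives the simulated probability that Lung is significant and Heart is not (20,000 trials per cell):

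| ρ | g = 0.3 | g = 0.5 | g = 0.7 |
|---|---|---|---|
| 0.3 | 15.8% | 19.7% | 9.5% |
| 0.5 | 13.8% | 16.4% | 8.4% |
| 0.7 | 10.0% | 12.3% | 6.5% |

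The interaction contrast rejected in 4.7-5.3% of the same trials.

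**Step 3: anatomy with s = 0.** The paired test within COPD has noncentrality d√40, with d the offset in SDs of the paired difference.

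- d = 0.3: 0.3 × 6.32 = 1.90, significant in 46% of trials.
- d = 0.5: 0.5 × 6.32 = 3.16, significant in 87% of trials.

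The interaction contrast again stays near 5%, because a cancels.

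**Step 4: precision of the interaction.** Var(Lung − Heart) = 2(1 − ρ)SD², which is no larger than SD² when ρ ≥ 0.5. At 80% power (normal approximation) the planned between-group test detects (1.96 + 0.84) × √(2/40) = 0.63 SD. Multiplying by √(2(1 − ρ)), the interaction detects 0.74, 0.63 and 0.49 SD at ρ = 0.3, 0.5 and 0.7.

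**Step 5: moxibustion.** Let c be a change common to both meridians, r an extra reactivity of the Lung midpoint under any stimulation, and s the effect of being the stimulated meridian.

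- Lung session, Lung minus Heart change: (c + r + s) − c = r + s.
- Heart session, Lung minus Heart change: (c + r) − (c + s) = r − s.
- Difference between sessions: 2s.

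A direct comparison of change in one session therefore removes c and any baseline offset, but not r. With s = 0 and 10,000 trials per scenario, it rejects in about 5% when r = 0 and in 35-98% when r = 0.3-0.5 SD (ρ 0.3-0.7). The two-session contrast rejects in 4.6-5.3%.

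**The case against.** **The t-test may already be the right one.** Section 2.11 does not say which variable enters the independent t-test. The Abstract's wording can be read as the Heart-Lung difference compared between groups, and a t-test on that difference is the interaction. A condensed article may leave the derived variable to the SAP. This reading is possible, but nothing fixes it. It also does not cure the Discussion's use of a Lung-Heart difference within COPD as support.

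**Hypothesis 2 is better placed.** A reader might infer that whole-body change and baseline anatomy undermine both hypotheses alike. The article does not support that. Moxibustion is given in one group, so no between-group test applies, and the Abstract and Discussion describe comparing change between meridians, which cancels both threats. What stands is that section 2.11 names no such test and that site reactivity remains in a single-session comparison.

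**No P-value rule is stated.** The phrase about more significant change could be taken as an instruction to compare P values. It is a hypothesis in a Discussion and probably means a larger change. The wording should be repaired, but it is not evidence of a planned P-value comparison.

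**Discordance is symmetric.** At g = 0.5 and ρ = 0.5, some discordance between meridians occurs in about 33% of trials. Half of that is Heart significant with Lung not, which contradicts the hypothesis. Only the 16% favours it, so 33% is not a bias towards the hypothesis.

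**The study is called an exploratory pilot.** That lowers the stakes but does not change which contrast answers the question.

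**Conclusion.** The concern holds for hypothesis 1. The article names tests and a supporting pattern that cannot separate Lung-meridian specificity from general desaturation or site anatomy. The false-support rates are about 6-20% (Lung significant, Heart not) and about 46-87% (within-COPD paired test), against about 5% for the interaction. These percentages rest on the assumed deficits, correlations and offsets and on 40 analysable participants per group. The direction follows from the algebra and does not depend on them.

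For hypothesis 2 the point is narrower: the intended comparison is described but not named as a test, and one session alone would count differing site reactivity as specificity.

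The interaction should not be taken as removing all confounding. If the sites differ in sensitivity to systemic desaturation (gL at Lung, gH at Heart), it estimates s − (gL − gH), and the 5% rate no longer holds.

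**What to change.** **Hypothesis 1.** State the primary test as the independent t-test, COPD versus healthy control, on each participant's mean Lung rSO2 (LU5, LU9) minus mean Heart rSO2 (HT3, HT7) over the 10-minute recording, or the equivalent mixed-model group-by-meridian term. Report a 95% CI. Keep the site-wise and within-group tests as descriptive, and do not take a Lung-Heart difference within COPD alone as support.

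**Hypothesis 2.** State the within-person stimulation-by-meridian contrast of change from the pre-moxibustion value over both sessions. Use only the Heart and Lung forearm midpoints: section 2.6.2 adds LU5 in one session and HT3 in the other, so the midpoints are the only sites common to both. Word the hypothesis as a larger change. The Abstract and Discussion place this comparison in the healthy control group, whereas section 2.6.2 applies moxibustion in the healthy intervention group; these passages must be reconciled so that the contrast names its group.

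**Cost.** Wording only: the same participants, sites, sessions and recordings. The interaction is somewhat less precise than the between-group test if the Lung-Heart correlation is below 0.5 (0.74 against 0.63 SD detectable at ρ = 0.3). Possible unequal site sensitivity to desaturation should be stated as a remaining limitation.
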